##### 1. Selecting Features Necessary to Examine Gaps in Quality

Data features will be identified from the enumerator collected survey tools during implementation. They may include (a) time to complete the overall questionnaire, select modules, and individuals questions, (b) frequency of enumerator selection of the response option ‘don’t know,’ and (c) skip patterns. While time-stamping all individual questions in the data collection tools will not be possible, select priority questions (eg, dietary recall) will be time-stamped, along with the start-stop times by module and for the overall time to complete the tool in its entirety. Data from enumerator collected survey tools during implementation will be linked with data on the enumerator profile and descriptive statistics used to identify outliers and as needed feedback data requiring follow-up. Each of these features and the indicator proposed to measure each is summarized in Table 1. Machine learning algorithms will ultimately be developed through the additional steps described below.

##### 2. Obtaining Labeled Data

Labeled data are essential in supervised machine learning. Labeled data can assume a variety of forms; in this case, we have data from enumerators completed on their own without a respondent as fast as they possibly can. These data are then labeled as ‘false’ data to be used in our supervised learning algorithms. By comparison, another labeled dataset will come from data captured during the pilot testing of tools. An alternative strategy for obtaining labeled data through data augmentation will also be explored. Data augmentation is the process of supplementing a dataset with similar data that is created from the information in that dataset.

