#### Data Analytics

Data analytics will focus on descriptive and outlier analyses.

Descriptive analyses will focus on the conduct of basic frequencies across all questions in the survey to ensure that questions are not being unexpectedly skipped. Beyond checking the frequencies across the variables, we will also examine any anomalies, such as incorrect unique identifiers or ineligible respondents based on date, every week. These frequencies will be examined after each district in the survey is halfway complete.

The outlier analysis aims to identify anomalies in the data, which could indicate gaps in quality. Outlier analysis will start with the selection of features, and depending on these features and their distributions (parametric/non-parametric), several techniques will be explored for outlier detection including numerical outliers, Z-score, linear models, probabilistic and statistical models, as well as unsupervised machine learning (k-means clustering). Analyses will draw from the following data sources: enumerator completed survey tools from piloting, enumerator completed survey tools from the main field implementation, enumerator profile survey, and the recheck survey. The following steps will be undertaken:

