##### 3. Building Models

This data will be split randomly into a training set and a testing set. As predictors of the models, we will use the features listed in step 1, and the data will be labeled as “false” or “true.”

Two steps will be undertaken to build models: (1) develop the best models for each learning algorithm using the training dataset and cross-validation methods and (2) apply the best performing algorithm on the test dataset for an unbiased evaluation. During the learning (training) process, k-fold cross-validation methods will be used to avoid overfitting and assess model performance. The k-fold cross-validation method involves splitting the dataset into k-subsets, which are, in turn, held out while the model is trained on all other subsets. The process is complete when accuracy has been determined for each instance in the data set, and an overall estimate of accuracy has been generated. Once the learning step is accomplished on the “training” set, we have trained models. Each model will be tested using the originally withheld testing set.

The algorithms under consideration are listed below in Table 2. We aim to train using all methods to identify the best algorithm for our data. Methods to assess the models, compare their attributes, and formulas to compare the results of the learning algorithms are similar to those presented in a study by Mohan et al [3]. That study also describes comparisons of the strengths of these various algorithms [3].

**Table 1 table1:** Biases in survey completion that can be captured using machine learning.

Biases	Indicator	Numerator	Denominator
Rushed completion	Percent of time to complete survey, sections, and individual question as compared to time recorded during piloting	Time measured during the pilot—actual time in seconds	Pilot time
CAPI^a^ entry error/ Fabricated responses	Percent difference from 10% resample	Questions that are different in 10% resample	Total number of questions resampled
Respondent bias	Mean time taken to complete questions among respondents in differing sociodemographic characteristics	N/A^b^	N/A
Skipping of sections	Percent of skips across all potential skip options throughout the tool	Opportunities where a skip was implemented	Total opportunities where a question or section can be skipped

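### If data augmentation is used in the written step order, synthetic records and their sources can fall on both sides of the train/test split, and the test evaluation would not be unbiased

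*Protocol article*

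**What the plan says.** The Data Analytics section of the protocol article introduces a numbered sequence with the words "The following steps will be undertaken".

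- **Step 2 (Obtaining Labeled Data)** names two real sources. For the 'false' label, "we have data from enumerators completed on their own without a respondent as fast as they possibly can". For comparison, "another labeled dataset will come from data captured during the pilot testing of tools". It then adds: "An alternative strategy for obtaining labeled data through data augmentation will also be explored". Augmentation is defined in the next sentence: "Data augmentation is the process of supplementing a dataset with similar data that is created from the information in that dataset".
- **Step 3 (Building Models)** opens with "This data will be split randomly into a training set and a testing set". Its second stage is to "apply the best performing algorithm on the test dataset for an unbiased evaluation". Cross-validation is described in the usual way: "k-fold cross-validation method involves splitting the dataset into k-subsets, which are, in turn, held out while the model is trained on all other subsets".

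Nowhere does the article give the number of labelled records, the type or ratio of augmentation, the split ratio, or k. It has no rule on where a derived record goes relative to its source.

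**The concern.** By the article's own definition, an augmented record is built from an existing one and is not independent of it. Step 2 treats augmentation as a way of obtaining labelled data, not as a device used during training. Step 3 then splits the data by simple randomisation. Carried out in that order, a real record can be used for training while its synthetic relative is used for testing, or the reverse. The same can happen between cross-validation folds. Measured accuracy would then partly reward recognition of near-copies, which is a different task from detecting a false interview.

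Two things are at stake. The first is the explicit claim that the test evaluation is unbiased. The second is the choice of algorithm. The plan trains all the methods in Table 2 to find the best one, and Table 2 mixes linear and flexible learners. Inflation that differs between them could affect the ranking as well as the reported accuracy. Quality gaps flagged by the chosen model may be fed back to field teams, and the Feedback Loops section lists responses that range up to re-interviewing a respondent.

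**Working it through.** **1. Reading the order.** The steps are numbered: features, then labelled data (with augmentation as an option), then split and modelling. The natural antecedent of the opening words of step 3 is whatever step 2 produced. If that includes augmented records, they are in the pool when it is split. Nothing confines them to the training part, keeps them with their source, or reserves the test set for real records.

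**2. No figure to reproduce.** The article reports no accuracy and no labelled-set size, so every setting below is an assumption. The field team has 35 enumerators (Field Coordination), which makes 35 'false' forms a plausible size. I take 35 records per class, 70 in all.

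**3. How often a test record would have a relative in training.** Assume a 70/30 split.
- 4 copies per record: pool = 70 × 5 = 350, training 245, test 105. For a given test record, the chance that all four relatives are also in the test set is (104 × 103 × 102 × 101) / (349 × 348 × 347 × 346) = 0.0076. So about 99% of test records have at least one relative in training.
- 1 copy per record: pool = 140, training 98, test 42. The chance that the one relative is in training is 98/139 = 0.71.

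**4. Effect on accuracy, simulation A.** 70 records, 5 normal features, signal on one feature, copies jittered with noise of 0.3 SD, 70/30 split, 40 to 60 replicates per cell.

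With no signal, correct accuracy is 50%. Augmenting before the split gives:

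| Copies | Random forest | CART | SVM | LDA |
|---|---|---|---|---|
| 4 | 81% | 74% | 76% | 57% |
| 1 | 68% | 64% | 64% | 53% |

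Splitting first gives 48–50%. With 4 copies the inflation is therefore 81 − 50 = 31 points for random forest and 57 − 50 = 7 for LDA.

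With 1 SD of signal and 4 copies, random forest shows 84% against 62% when the split comes first (+22). LDA shows 69% against 63% (+6).

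With stronger separation and 4 copies, accuracy minus accuracy on 1000 fresh real records, in points:

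| Separation | Random forest | CART | SVM | LDA |
|---|---|---|---|---|
| 2 SD | +9 | +11 | +9 | +1 |
| 3 SD | +4 | +4 | +3 | +1 |
| 4 SD | +1 | +2 | +1 | 0 |
| 5 SD | <1 | <1 | <1 | <1 |

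**5. Effect on accuracy, simulation B.** 10 features, 35 or 70 records per class, separation 0 to 4 SD, 1 or 4 copies, 200 runs per cell. The learners were LDA and 1-nearest-neighbour; the latter is not in Table 2 and stands in as a worst case for learners that memorise.
- LDA: from 0.975 − 0.972 = +0.3 points (4 SD, 70 per class, 4 copies) to 0.613 − 0.500 = +11 points (no signal, 35 per class, 4 copies).
- 1-nearest-neighbour: from 0.981 − 0.942 = +4 points (4 SD, 70 per class, 1 copy) to 0.993 − 0.500 = +49 points (no signal, 35 per class, 4 copies).
- Bias was upward in every cell.

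**6. Effect of reversing the order.** In simulation B, when the split came first and only the training part was augmented, test accuracy agreed with accuracy on fresh records to within about 2 points in every cell. For example, at 2 SD, 35 per class and 4 copies, LDA gave 0.794 against 0.806, where augmenting first had given 0.853.

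**The case against.** A reader might infer that the plan commits to pooling synthetic records before the split, and that its accuracy will therefore be inflated. The text does not support this. Augmentation is an alternative to be explored beside two real sources, and no sentence expressly says when it happens. The opening words of step 3 could refer to the two firm data sets alone. Step 3 later describes the test set as having been withheld at the outset, which fits a reserve of original records but does not settle the order. If augmentation is not used, or is applied only to training data, this leak does not arise. That stands, and it makes the point conditional.

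A reader might also infer that inflation of about 30 points, or a false advantage for random forest, is to be expected. The simulations show these only where the classes are weakly separated. In the plan, the 'false' forms are filled at top speed without a respondent, interviews average about 1.5 hours, and completion time is a named feature. Separation on time may well be large, although the article gives no figure for it. At 4 SD or more, little bias remains in simulation A. This stands too, and it limits the size that can be claimed.

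Finally, it can be said that handling within folds belongs in a fuller analysis plan, which is not shown. That would answer a complaint about missing detail. It does not fully answer this one, because the article itself sets the step order, specifies a simple random split and claims an unbiased result. Following that order with the option it offers would defeat the claim.

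**Conclusion.** The point holds in conditional form. If augmentation is used and the steps are followed as numbered, derived and source records can sit on both sides of the train/test split and of the cross-validation folds, and the evaluation would not be unbiased. The direction is upward, and the bias is greater for flexible learners than for linear ones.

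The size cannot be derived from the article. It depends on the number of records, the type and number of synthetic copies, the learner and the class separation. In the 5-feature, 4-copy setting, inflation for random forest falls from 31 points with no signal to about 1 to 2 at 4 SD, and LDA is inflated by at most about 7. With 10 features, LDA reached about 11. A material effect on the choice of algorithm is a possibility under weak separation, not an established consequence.

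**What to change.** State in steps 2 and 3 that:

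1. the original labelled records are divided into training and testing sets first;
2. if augmentation is used, synthetic records are generated only from the training part and, during cross-validation, only from the k−1 training folds;
3. all reported accuracy, cross-validated and test, is computed on original records only.

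This costs a sentence or two of text and a reordering of code, with no new data. The downsides are a possibly lower reported accuracy and a test set limited to the original records, so its accuracy estimate may be less precise.

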##### 3. Building Models

This data will be split randomly into a training set and a testing set. As predictors of the models, we will use the features listed in step 1, and the data will be labeled as “false” or “true.”

Two steps will be undertaken to build models: (1) develop the best models for each learning algorithm using the training dataset and cross-validation methods and (2) apply the best performing algorithm on the test dataset for an unbiased evaluation. During the learning (training) process, k-fold cross-validation methods will be used to avoid overfitting and assess model performance. The k-fold cross-validation method involves splitting the dataset into k-subsets, which are, in turn, held out while the model is trained on all other subsets. The process is complete when accuracy has been determined for each instance in the data set, and an overall estimate of accuracy has been generated. Once the learning step is accomplished on the “training” set, we have trained models. Each model will be tested using the originally withheld testing set.

The algorithms under consideration are listed below in Table 2. We aim to train using all methods to identify the best algorithm for our data. Methods to assess the models, compare their attributes, and formulas to compare the results of the learning algorithms are similar to those presented in a study by Mohan et al [3]. That study also describes comparisons of the strengths of these various algorithms [3].

**Table 1 table1:** Biases in survey completion that can be captured using machine learning.

Biases	Indicator	Numerator	Denominator
Rushed completion	Percent of time to complete survey, sections, and individual question as compared to time recorded during piloting	Time measured during the pilot—actual time in seconds	Pilot time
CAPI^a^ entry error/ Fabricated responses	Percent difference from 10% resample	Questions that are different in 10% resample	Total number of questions resampled
Respondent bias	Mean time taken to complete questions among respondents in differing sociodemographic characteristics	N/A^b^	N/A
Skipping of sections	Percent of skips across all potential skip options throughout the tool	Opportunities where a skip was implemented	Total opportunities where a question or section can be skipped
Misunderstanding of content	Percent of “don’t knows” across all questions and by section per respondent or enumerator	Questions with “don’t know” answers	Total number of questions with “don’t know” options

^a^CAPI: computer-assisted personal interviewing.

^b^N/A: not applicable.

**Table 2 table2:** Machine learning algorithms.

Algorithm		Description	Intended application

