During training, we spent time reviewing the paper versions of the tool as well as ensuring that our CAPI tablet versions, programmed using CSPro software, mirrored them well and adhered to the skip logic we had outlined. Both paper and tablet versions of the survey took on average about 1.5 hours to complete. The tablet version of the survey had just one question at a time appear on the screen. The process of checking the tablet version of the tool continued before and after piloting these versions in the field to ensure we had made all necessary changes in both language and logic before data collection with our end-line sample began. All survey data will be collected on tablets.

As part of the tablet-based data collection forms, we added a few parameters that were not part of the paper tools. These included time-stamps for the start and end of modules and time flags at the beginning and end of questions involving in-depth probing. GPS fields were added to the end of the tablet-based tool to track location.

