The limitations of this approach include the parameters used for the machine learning approach—ideally more time-stamps and information on tapping forward or back off a screen would provide more detail on the timing and mechanics of each survey completed. In some cases, an interview may be interrupted by factors outside the enumerator’s and respondent’s control such as a baby crying or a neighbor calling; however, the enumerators are encouraged to do their best to complete the survey in one sitting and include comments on hindering circumstances that extend the length of the interview at the end of the survey. Additionally, some skips in the surveys and “don’t know” responses are necessary and unavoidable; thus, these measures could be ambiguous at times. Given the nature of our multi-select tool, we expected enumerators to be probing for answers and using “other specify” for ambiguous answers and using the “don’t know” option minimally. However, this parameter is specific to our survey, and it could be that in another type of tool, other parameters are used to indicate rushed or low-quality interviews. This difference is true of other steps as well, such as which time-stamps to collect, what kind of labeled data to obtain, and the types of responses that are useful for quality control. Quality assurance needs to be tailored for each survey.

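### The rushed-completion score in Table 1 compares raw time with pilot time and ignores how many questions the skip logic asked, so it cannot tell routing from pace

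*Protocol article*

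**What the plan says.** Table 1 (under 3. Building Models) measures rushed completion by "Percent of time to complete survey, sections, and individual question as compared to time recorded during piloting". The numerator is "Time measured during the pilot—actual time in seconds" and the denominator is the pilot time. The respondent-bias row is "Mean time taken to complete questions among respondents in differing sociodemographic characteristics", with numerator and denominator marked as not applicable.

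The times available are described in two places. Under Tool Development, the tablet form carries "time-stamps for the start and end of modules and time flags at the beginning and end of questions involving in-depth probing". Under 1. Selecting Features, the article says "While time-stamping all individual questions in the data collection tools will not be possible", but "select priority questions (eg, dietary recall) will be time-stamped, along with the start-stop times by module", together with the overall time.

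The tool has conditional routing: the tablet version was checked to see that it "adhered to the skip logic we had outlined". Skips have their own row in Table 1, and Table 2 lists times, don't-knows and skips together as inputs to each algorithm. The Discussion concedes that "some skips in the surveys and “don’t know” responses are necessary and unavoidable". It draws the consequence of ambiguity for those two measures and does not extend it to time.

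**The concern.** In a survey with skip logic, interview length depends on two things: how many questions are asked, and how long each one takes. Only the second is evidence of rushing. The printed formula contains the first but does not adjust for it. A woman correctly routed past part of a module raises the score, and an enumerator who hurries a woman on a long path is partly hidden.

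This matters because time is also used outside the fitted models. Under Field Monitoring, the back-end data quality supervisor looks at completion time and at skip and don't-know rates to decide which enumerators to observe further. Under 1. Selecting Features, descriptive statistics on these features are used to find outliers for follow-up. Under Feedback Loops, the response can go as far as retraining or, in serious cases, a repeat interview. Inside the supervised models, the false class comes from forms that enumerators filled in without a respondent at top speed. Short total time is therefore likely to be learned as a sign of falsification, whatever its cause.

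The respondent-bias row has the same weakness if it is computed from total times. Groups routed to different numbers of questions would differ in mean time even if they were interviewed at the same pace.

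**Working it through.** The article reports no value for this indicator, so there is no figure to reproduce. The check applies the printed formula.

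**Inputs**
- Pilot time T = 5400 s, from the average of about 1.5 hours given under Tool Development (1.5 × 3600). It serves only as an illustration; T cancels from the score.
- s = share fewer questions asked than in the average pilot interview (negative if more are asked). This is assumed, with a range of 0 to 40%, because the article gives neither question counts nor skip frequencies.
- r = reduction in time per question relative to the pilot, also assumed.
- Time per question is taken as equal across questions.

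**Formulas**
- Actual time: A = T(1 − s)(1 − r)
- Table 1 score: I = (T − A)/T = 1 − (1 − s)(1 − r)
- Score per question asked: J = 1 − [A/(1 − s)]/T = r

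**Unchanged pace (r = 0), fewer questions**

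| s | A (s) | I (Table 1) | J (per question) |
|---|---|---|---|
| 0% | 5400 | 0% | 0% |
| 10% | 4860 | 10% | 0% |
| 20% | 4320 | 20% | 0% |
| 30% | 3780 | 30% | 0% |
| 40% | 3240 | 40% | 0% |

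At an unchanged pace, the Table 1 score equals the share of questions routed past.

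**Faster pace, same routing.** With s = 0 and r = 20%, A = 5400 × 0.8 = 4320 s, so I = 20% and J = 20%. Table 1 gives the same value as for s = 20% with no rushing.

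**Faster pace, longer path.** With s = −20% and r = 20%, A = 5400 × 1.2 × 0.8 = 5184 s. Then I = (5400 − 5184)/5400 = 4%, while J = 20%.

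**Respondent bias.** Take two groups interviewed at the same pace, one of them routed to 10% fewer questions. Their mean total times are 5400 s and 4860 s, a gap of 540 s that comes from routing alone.

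**Limit of the per-question score.** Suppose an enumerator shortens the interview by entering false answers at gate questions, so that 20% of the questions never appear, and keeps the pilot pace on the rest. Then I = 20% but J = 0%. Raw time sees this and pace alone does not.

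**The case against.** **Question-level times.** A reader might infer that Table 1 asks for question times the tablet never records, so that its rows cannot be computed. The article does not support this. Selected priority and probing questions are stamped, the limit is stated in the section that introduces Table 1, and the Discussion lists it again. The reference to individual questions can naturally be read as meaning the stamped ones.

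**No flagging rule.** A reader might also infer that correctly routed women are classified as rushed. Table 1 gives a continuous percentage with no cut-off, several outlier techniques are to be explored, and the survey coordinator judges the response. The point is a higher score, not a stated misclassification. Nor does rushing on a long path always look normal: it is masked to a degree that depends on s and r.

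**Skips are already in the models.** This is the strongest objection. With both times and skips as predictors, a model can discount short times that come with many skips. That may help in part. However, the skip row is one tool-wide percentage of skip opportunities, and an opportunity may be a single question or a whole section. It is therefore not a count of questions asked and cannot rescale a module time. It also does not separate legitimate from improper skips, so a correctly routed woman scores higher on both rows. The descriptive uses of time get no such adjustment.

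**Averaging.** With 5095 women and 35 enumerators there are about 146 interviews each (5095/35), so routing largely averages out at enumerator level unless it differs systematically between enumerators. That is fair, but it does not help scores for single interviews. The pilot villages resembled the study population, so the pilot time already includes typical routing. The working allows for this by defining s relative to the pilot average.

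**Respondent-bias row.** It can be read as time per question or as time on stamped questions, and either reading avoids most of the problem. The row does not say which is meant.

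**Conclusion.** The point stands in a limited form. As printed, the survey-level and section-level rushing score has no term for the number of questions asked, and it cannot distinguish correct routing from a faster pace. A 20% shorter path and a 20% faster pace both score 20%; a 20% longer path with a 20% faster pace scores 4%. The caveat in the Discussion covers skips and don't-knows, not time.

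The algebra needs only the printed formula and equal time per question. The size in this survey is unknown: the 0 to 40% range is assumed, no threshold is fixed, and joint modelling may absorb some of the effect. This is a weakness in how one feature is defined. It does not make the indicator uncomputable, and the article does not contradict itself on it.

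**What to change.** Keep raw time and add a second time feature beside it: survey time and module time divided by the number of questions actually asked. That number can be derived from the recorded answers and the skip logic. Benchmark the feature to the same quantity in the pilot interviews.

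Read pace, raw time and the skip indicator together. Replacing raw time outright would hide an interview shortened through false gate answers. With all three in view, such an interview still shows as a short raw time and a high skip percentage at a normal pace.

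For the respondent-bias row, state that it uses the per-question pace or the time on stamped questions. In the rushed-completion row, say that individual questions means the stamped ones.

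The cost is one derived variable and a rewording of two rows in Table 1; no new data collection is needed. A small downside is that average pace ignores differences in question length within a module, so an interview with many probing items will look slower than one made up of short closed items.
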